### ③Cancellation criteria

Clinical research will be discontinued if any of the following applies.

- During the test period, the subject develops serious symptoms and the safety of the supplement becomes questionable.
- When it becomes clear that the subject was affected by continuously consuming the supplement.

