## 3. Method

- 1) Survey period: 12 weeks (August 2017-February 2018)
- 2) Test method: Epidemiological survey, clinical trial (randomized open trial)
- 3) Number of cases: 60 cases (30 women who take equol + lactobionic acid supplement, and 30 women who do not take the supplement)
- 4) Test food: "Equol + lactobionic acid" 3 tablets (10 mg) daily (marketed in December 2013)

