## 5. Outcome evaluation

- 1) Primary Outcomes: blood test (TG, HDL-C, LDL-C, T-CL, uric acid, HbA1C), baPWV, visceral fat area
- 2) Key Secondary Outcomes: AGE, relationship between equol-producing ability, type of intestinal bacteria, and dietary habit assessment (BDHQ) from the test results, safety of supplement, climacteric symptoms

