## 7. Analysis

For the primary measures, perform chi-squared test and t test for comparison between groups and before and after the study period. For secondary outcomes, anonymized data are entered into the database and the correlation is analyzed. Drop out cases and missing values are not included in the analysis. Other questionnaire surveys will be conducted according to the evaluation criteria of each questionnaire. The visceral fat CT examination and baPWV measurement at the start of the test and at 12 weeks will be performed at the same site in order to eliminate measurement errors.

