### 3) Recording and investigation of adverse events

If an adverse event occurs, its symptoms or disease, content of objective findings, date of onset, degree,

severity, presence or absence of treatment and its content, outcome and date of diagnosis, relevance to this clinical study and the underlying reason are to be recorded in the adverse event section of the case report. When the name of the disease is described, the symptom associated with the disease is not recorded as an adverse event.

If an adverse event is observed in the symptoms, diseases, or objective findings observed during the treatment period, it will be followed up until the condition become normalized or improved up to a level that could not be regarded as an adverse event, regardless of whether it has a causal relationship with this clinical study. However, this does not apply if the investigator determines that the patient has recovered. In that case, the grounds for determining recovery shall be stated in the case report form. If irreversible adverse events are observed due to organic disorders (cerebral infarction, myocardial infarction, etc.), follow-up will be conducted until the symptoms stabilize or improve.

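### The rule that removes drop-outs from the analysis makes no exception for safety, so a woman who stops because of an adverse event can leave the analysed safety result

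*Protocol*

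**What the plan says.** Section 5 (Outcome evaluation) ends its list of key secondary outcomes with "safety of supplement, climacteric symptoms".

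Section 7 is the protocol's only analysis section. It first names the tests for the primary measures. It then says: "For secondary outcomes, anonymized data are entered into the database and the correlation is analyzed". The next sentence is "Drop out cases and missing values are not included in the analysis". That sentence names no outcome and no exception, and no other section names a safety population.

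Section 2, under the cancellation criteria, gives two grounds for discontinuation: "During the test period, the subject develops serious symptoms and the safety of the supplement becomes questionable" and "When it becomes clear that the subject was affected by continuously consuming the supplement". Section 11, 3), item ⑨ lets a woman withdraw at any time.

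Section 9, 3) covers the handling of events. Their details "are to be recorded in the adverse event section of the case report", and each event is followed until it normalises or improves, "regardless of whether it has a causal relationship with this clinical study". The schedule in section 6 has safety monitoring at weeks 0, 4, 8 and 12.

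Section 3 plans "60 cases (30 women who take equol + lactobionic acid supplement, and 30 women who do not take the supplement").

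**The concern.** A safety outcome exists to count unwanted events in the women exposed. A rule that removes drop-outs works against this when the event is the reason for dropping out. Both cancellation grounds are themselves safety events, and a woman who feels unwell on the tablets may also withdraw of her own accord. If these women are removed and women with milder events stay in, the analysed result keeps the tolerated events and loses those that led to stopping.

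This is a separate problem from what deletion does to the randomised comparison of the primary measures. Analysing those measures in all randomised women would leave the safety result as it is, because safety needs its own statement of who is counted.

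With about 30 women on supplement, one removed case can turn an observed event into a report of none.

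**Working it through.** The protocol states no safety figure, so there is none to reproduce. The check has three parts.

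**1. Does the rule reach safety?** Safety is a secondary outcome (section 5). The deletion sentence follows the sentence on secondary outcomes and refers to the analysis without qualification (section 7). Section 9 says which events are recorded and how long they are followed. It does not say that events in drop-outs enter the safety result. As written, the rule covers safety.

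**2. Which way does deletion push the proportion?** Let an arm have n women, E of them with an event. Let k women drop out, j of them with an event. All women counted gives E/n. Drop-outs deleted gives (E − j)/(n − k). Cross-multiplying,

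(E − j)/(n − k) < E/n exactly when j/k > E/n.

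So deletion understates the proportion when events are more common among drop-outs than in the arm as a whole. That is the case when women leave because of events, unless every woman in the arm has one. It overstates the proportion when the drop-outs are event-free and some completers have events.

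**3. Size, for illustration.** The input from the protocol is n = 30 on supplement (section 3). The numbers stopped and the event counts are assumptions, and so is the use of a simple proportion of women with an event. Intervals are exact (Clopper-Pearson): lower limit = 2.5% quantile of Beta(x, n − x + 1), upper limit = 97.5% quantile of Beta(x + 1, n − x). For x = 0 the lower limit is 0 and the upper limit is 1 − 0.025^(1/n).

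If k women stop because of an event and no other woman has one:

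| k | All 30 counted (95% CI) | Drop-outs deleted (95% CI) |
|---|---|---|
| 0 | 0/30 = 0% (0 to 11.6%) | 0/30 = 0% (0 to 11.6%) |
| 1 | 1/30 = 3.3% (0.1 to 17.2%) | 0/29 = 0% (0 to 11.9%) |
| 2 | 2/30 = 6.7% (0.8 to 22.1%) | 0/28 = 0% (0 to 12.3%) |
| 3 | 3/30 = 10.0% (2.1 to 26.5%) | 0/27 = 0% (0 to 12.8%) |

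Two further cases, each with 2 completers who have an event:

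- 3 women stop because of an event: 5/30 = 16.7% with all counted, 2/27 = 7.4% with drop-outs deleted. Here j/k = 3/3 exceeds 5/30, so the proportion falls.
- 3 event-free women drop out: 2/30 = 6.7% with all counted, 2/27 = 7.4% with drop-outs deleted. Here j/k = 0, so the proportion rises.

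The chance that at least one of 30 women stops because of an event is 1 − (1 − p)^30. For assumed p of 1%, 3%, 5% and 10% this is 26%, 60%, 79% and 96%. The protocol gives no p. Its only statement on frequency is that allergic symptoms may appear rarely (section 8).

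**The case against.** The strongest reply is that the protocol never says that a woman stopped for an event is removed from the safety result. The cancellation criteria speak of the clinical research being discontinued, which could mean the whole study. Drop-out is not defined. Section 9 keeps a woman under follow-up for her event, so she is not plainly lost for safety. The deletion sentence comes after t tests, chi-squared tests and correlations, and may be meant only for those. No safety proportion or denominator is defined, and naming a safety population is commonly left to the SAP, which is not shown.

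Much of this stands as a limit on the claim. A reader might infer that the protocol expressly deletes stopped women. It does not; that is the natural reading, since the criteria sit among the selection and exclusion criteria for subjects and refer to the subject. But the point does not depend on it. A woman who withdraws because of an event under section 11 is a drop-out on either reading of the cancellation criteria. Section 9 protects the record of her event, not its place in the result. And the point is not that a safety population is missing. The protocol states a general rule that, as worded, covers a key secondary outcome, and an SAP that followed the rule would inherit the problem.

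A reader might also infer that the safety result is bound to be biased in the supplement's favour. The documents do not support that. The rule removes event-free drop-outs as well, which raises the proportion, and it removes control drop-outs, so the direction of the difference between arms is not fixed.

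**Conclusion.** The point holds in a conditional form. The deletion sentence as worded applies to safety, and where women leave because of events it understates the event proportion in the supplement arm. The size cannot be stated, because the protocol gives no drop-out rate and no adverse event rate. The effect is nil if no woman stops for an event. The contrast of 0% with 3.3%, 6.7% or 10.0% for 1, 2 or 3 such women is arithmetic on assumed counts and not a forecast; it also supposes that no completer has an event.

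It would go too far to say that the supplement will appear safer than it is, or that events are lost. The loss is in the analysed result, not in data capture. The sentence should be corrected because it can distort a key outcome and costs almost nothing to repair.

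**What to change.** In section 7, limit the deletion sentence so that it does not apply to safety. Add that adverse events are summarised by arm in all allocated women (in the supplement arm, all who took at least one dose), including those who stopped early, and that discontinuations for adverse events are reported by arm. The same edit can say what counts as a drop-out for the analysis, without touching any rule on when intake or the study stops. If an SAP exists, its wording should match.

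The cost is one or two sentences. No new data are needed, because section 9 already has events recorded and followed up and section 6 already schedules safety monitoring at weeks 4 and 8. The downside is a possibly less favourable safety figure.

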#### 5) Protection of personal information

Protect the personal information of subjects when conducting clinical trials.

In protecting personal information, all data related to this protocol should be anonymized (coded) and handled. Information that can be identifiable personally will be stored and managed in a place where it can be locked under the strict control of the person in-charge of personal information management at the Sendai General Medical Examination Clinic. When it is no longer needed, dispose of it in an irreproducible form such as incineration or dissolution. In the unlikely event that personal information is leaked, the following measures will be taken promptly.

-Fact-finding, investigation of cause

-Identify the range of influence

-Examination and implementation of recurrence prevention measures

-Contacting potential affected individuals

-Report to the Minister of Health, Labor and Welfare

-Publication of facts, recurrence prevention measures, etc.

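### Measuring at the same site cannot eliminate error in CT visceral fat area, a primary outcome of this open trial, and no masking of the reader to arm or visit is stated

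*Protocol*

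**What the plan says.** Protocol section 3 (Method) describes the design as a "clinical trial (randomized open trial") with "30 women who take equol + lactobionic acid supplement, and 30 women who do not take the supplement". There is no placebo.

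Section 5 lists eight primary measures, "Primary Outcomes: blood test (TG, HDL-C, LDL-C, T-CL, uric acid, HbA1C), baPWV, visceral fat area". The schedule in section 6 places the fat scan and baPWV at week 0 and week 12.

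Section 7 plans to "perform chi-squared test and t test for comparison between groups and before and after the study period" for the primary measures. It then says that the fat CT and baPWV at the two visits "will be performed at the same site in order to eliminate measurement errors". This is the only provision in the available text on the quality of these two measurements.

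Section 11, item 5, says that "all data related to this protocol should be anonymized (coded) and handled". It stands under the protection of personal information.

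**The concern.** The sentence in section 7 treats measurement error as dealt with. Using one facility removes differences between facilities and their equipment. Using one anatomical location removes some variation in where the image is taken. Neither removes the remaining random error, and neither controls what the reader knows.

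Two kinds of knowledge matter, and they act on different tests:

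- **Arm.** A reader who knows the allocation can read week-12 scans differently in the two groups. That goes straight into the between-group comparison.
- **Visit.** A reader who knows only the visit would tend to shift both arms alike, which largely cancels when changes are compared between groups. It does not cancel in the before-after tests that section 7 also plans.

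Bias of either kind sits in the recorded values, and no later analysis can take it out. Masking of readers is therefore a matter of trial conduct that belongs in the protocol and cannot be supplied by an analysis plan.

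**Working it through.** **1. What the text establishes.** The protocol gives no figure for measurement error, reader agreement or bias, so there is nothing of its own to reproduce. Set side by side:

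| Question | Where | Answer |
|---|---|---|
| Is allocation open? | Section 3 | Yes, with an untreated control |
| Is CT fat area primary? | Section 5 | Yes |
| What protects its measurement? | Section 7 | Same site at both visits |
| Is the reader masked to arm or visit? | Nowhere in the available text | Not stated |
| Does coding of data mask the reader? | Section 11, item 5 | It is a privacy measure |
| Does anonymized entry mask the reader? | Section 7 | It is stated for secondary outcomes, at database entry, after measurement |

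**2. How much a shift could matter (illustration only).**

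From the protocol: 30 women per arm.

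Assumed: two-sided 5% level; all 30 per arm analysed; no true effect; a t test on change scores (section 7 does not fix this); baseline-to-week-12 correlation r of 0.5, 0.8 or 0.9; arm-differential reading shift b of 0.05, 0.10 or 0.20 cross-sectional SD.

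In cross-sectional SD units with equal variances, SD of change = √(2(1 − r)):

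- r = 0.5: √1.0 = 1.000
- r = 0.8: √0.4 = 0.632
- r = 0.9: √0.2 = 0.447

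The two-sample t statistic has 58 degrees of freedom and noncentrality (b / SD of change) / √(2/30), with √(2/30) = 0.258. For example, b = 0.10 and r = 0.9 give (0.10 / 0.447) / 0.258 = 0.866, and a rejection rate of 13.6%.

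Between-group false-positive rate:

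| r | b = 0.05 | b = 0.10 | b = 0.20 |
|---|---|---|---|
| 0.5 | 5.4% | 6.7% | 11.9% |
| 0.8 | 6.0% | 9.2% | 22.6% |
| 0.9 | 7.1% | 13.6% | 39.9% |

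If only week-12 values were compared, the relevant SD would be 1 and the first row would apply whatever r is.

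**3. Visit-only knowledge.** For a paired t test in one arm (n = 30, 29 degrees of freedom), the noncentrality is (b / SD of change) × √30. A visit-related shift of 0.05, 0.10 or 0.20 SD at r = 0.9 gives 9.1%, 22.0% and 65.8%. At r = 0.5 the figures are 5.8%, 8.3% and 18.5%. The before-after tests are thus more sensitive than the between-group test to a shift of the same size.

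**The case against.** The strongest case on the other side is that the mechanism is not in the documents. Section 4 names only a CT fat scan. Nothing says whether the reading is manual, semi-automatic or automatic, and an automated reading would leave little room for bias. The reference list includes a paper on a standardized CT technique, which hints at a fixed method. Nor does the text say who reads the scans or whether that person learns the allocation, and the sections on location and staff are not in the public text.

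Most of this stands. It limits the point to a stated safeguard that cannot do what is claimed for it, with no masking stated in the available text. It does not rescue the claim to eliminate error. The available text does not invoke the cited technique as a procedure, and standardizing a measurement does not mask the person making it.

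The phrase about the same site is also ambiguous. If it means anatomical location, it partly addresses variation in slice position, but it still provides no masking.

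A reader might infer three stronger things that the documents do not support:

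- **That the error rate will reach 40%.** That is the most extreme cell of an assumed grid. At r = 0.5 the same shift gives 12%, and the smallest shift barely moves the rate at any of the three correlations.
- **That baPWV is equally exposed.** The protocol describes no route by which an operator could influence it.
- **That the primary results as a whole are compromised.** Six of the eight primary measures are blood tests.

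**Conclusion.** The point holds as a modest, inexpensive improvement. Section 7 is wrong to say that measuring at the same site eliminates measurement error, and the available text states no masking for the CT reading of a primary outcome in an open trial. Lack of masking to arm matters for the between-group test. Lack of masking to visit matters mainly for the before-after tests.

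The size of any bias is unknown. Over the assumed grid, the between-group error rate runs from about 5% (shift 0.05 SD, r = 0.5) to about 40% (shift 0.20 SD, r = 0.9). These figures rest wholly on assumed shifts and correlations and on a change-score t test. They show that a small differential shift could matter if week-0 and week-12 values are highly correlated. They do not show that such a shift occurs.

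**What to change.** In section 7:

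1. Replace *eliminate* with *reduce*, and say whether *site* means the facility or the anatomical location.
2. State that each woman's week-0 and week-12 CT images are stored under study codes and read by the same existing reader after her week-12 visit, in random order, with arm and visit hidden.
3. As a lesser measure, state that the allocation is not given to the baPWV operator. This is only partial, because a participant who knows her group may disclose it.

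The cost is relabelling image files and batching the reads. No extra visit, scan or reader is needed. The downside is that fat-area results, which the section 6 schedule includes in the result report, reach participants slightly later.

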## 8. Expected adverse events

In rare cases, allergic symptoms to supplement may appear.

## 9. Handling of adverse events

### 1) Symptoms or disease

Any unfavorable or unintended signs, symptoms or disease that develops during the study is treated as an adverse event. However, worsening of biomedical parameters in the study will not be treated as an adverse event.

### 2) Objective findings

If abnormalities or deterioration (normal → abnormal / worse, abnormal / worse → more abnormal / worser) are detected after the study period compared to before the study, it is treated as an adverse event. Regardless of the items specified or unspecified in this protocol, those considered to be adverse events need to be recorded in the case report, describing the onset, time of maximum severity, outcome, and relevance.

### 3) Recording and investigation of adverse events

If an adverse event occurs, its symptoms or disease, content of objective findings, date of onset, degree,

severity, presence or absence of treatment and its content, outcome and date of diagnosis, relevance to this clinical study and the underlying reason are to be recorded in the adverse event section of the case report. When the name of the disease is described, the symptom associated with the disease is not recorded as an adverse event.

If an adverse event is observed in the symptoms, diseases, or objective findings observed during the treatment period, it will be followed up until the condition become normalized or improved up to a level that could not be regarded as an adverse event, regardless of whether it has a causal relationship with this clinical study. However, this does not apply if the investigator determines that the patient has recovered. In that case, the grounds for determining recovery shall be stated in the case report form. If irreversible adverse events are observed due to organic disorders (cerebral infarction, myocardial infarction, etc.), follow-up will be conducted until the symptoms stabilize or improve.

#### 4) Classification of adverse events

The degree of adverse events is classified according to the following criteria.

- ① Mild: To the extent that the subject's daily life is not impaired
- ② Moderate: It interferes with the subject's daily life, but if he / she puts up with it, he / she can carry out the activity.
- ③Altitude: Degree that greatly interferes with the subject's daily activities

Adverse event outcomes are classified according to the following criteria:

- ① Recovery: Normalization or recovery to a level that cannot be regarded as an adverse event
- ②Continuation: Those that have not recovered at that time
- ③Unknown (death): The outcome was unknown due to the death of the patient

#### 5) Judgment of the relationship between adverse events and this clinical study

The relevance to this clinical study will be determined according to the following relevance criteria, taking into consideration the condition of the subject, the time relationship with treatment, and the possibility of other factors.

- ①Obviously related
- ② Probably related
- ③ May be related
- ④ Not related

Regarding adverse events, items ①to ③) are those whose relevance to this clinical study cannot be ruled out, and item ④is regarded as an adverse event whose relevance to this clinical study is denied.

#### 6) Serious adverse events

If a serious adverse event occurs during the study period, whether or not it has a causal relationship with this clinical study, the investigator will immediately give an appropriate treatment to the subject.

#### 7) Providing new information

When new information on the safety of this clinical study is obtained, the explanatory document and consent document will be revised promptly as necessary.

## **10. Medical expenses and compensation**

### **1) Medical expenses**

- The cost of the first regular medical examination will be borne by the patient, and if it is clear that it is related to this clinical trial, the patient will not be liable for the cost. If it is unclear, it will be decided through consultation.
- If medical expenses are incurred, the research implementation facility, Sendai General Health Examination Clinic, and Advanced Medical Care Co., Ltd., the sponsor company, will deal with them upon discussion.

